**Sample Size and Power.** For the primary/secondary efficacy outcomes, HbA1c (Primary) and BP/QOL (Secondary), with 18 subjects randomized to each of the three intervention groups, we will have 85% power to detect at least a 1.0 standardized effect size (difference in within group means in sd units). This calculation assumes that the primary/secondary efficacy outcomes are measured at 2 time points (baseline and 3-months); the intra-class correlation for repeated observations is no greater than 0.5; level of significance ( $\alpha$ ) =0.05, two-tailed test. Assuming that HbA1c measurements have a standard deviation of approximately 1.5 based on our pilot studies, the study has 85% power to detect a difference of 1.0 percentage points (raw units) change in HbA1c within each of the three comparisons groups. Analyses for continuous secondary/exploratory outcomes (behavioral and process variables) also have 85% power to detect a standardized effect size of 1.0sd. To account for the "fraction of missing" information that must be imputed in the ITT sample and the dilution effect of ITT analyses (Hsieh et al., 2003) the sample size is inflated by 10% to achieve a final ITT sample size of 20 subjects randomized to each treatment group (N=60).

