## Data Analysis

### Design/Analysis Issues

Analysis sets. The intent-to-treat (ITT) sample, comprising all randomized patients, will be used for the primary analyses. The per protocol/completer sample will comprise subjects who were compliant with protocol requirements and for whom all required measurements over 3-months of follow-up have been made. Analyses will be carried out separately for ITT and per protocol samples to test sensitivity of conclusions to drop-outs/nonadherence. If differences are present between the per protocol and ITT analysis sets, the characteristics of the two analysis populations will be examined to aid in explaining any discrepancies.

**Analysis Plan for Primary Aim (Efficacy):** To test the efficacy of three financial incentive structures in combination with technology intensified diabetes education and skills training intervention on HbA1c levels in AAs with T2DM. Preliminary analyses will be conducted to assess the similarity of the treatment arms based on collected variables. Univariate descriptive statistics and frequency distributions will be calculated, as appropriate for all variables along with two-sided 95% confidence intervals when appropriate. Study discontinuation (attrition) rates will be estimated for each group. The preliminary analyses will describe the pre-specified covariates as well as identify potential confounding (prognostic) variables to be used as covariates in subsequent secondary analyses. Covariates to be examined in the preliminary analyses and potentially used in secondary analyses include age, sex, income, health literacy, social support, depression, and comorbidity. The primary framework for analysis is paired t-test. Change in HbA1c from baseline to 3-months (dependent variable) will be examined in each treatment arm (high, moderate and low frequency of financial incentives) using a type I error rate of 0.05.

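### The power statement caps the correlation at 0.5, but a paired test on change needs a minimum; 1.0 HbA1c point has at most about 76% power within that cap, not 85%

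*Protocol*

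**What the plan says.** The protocol's Sample Size and Power paragraph bases its calculation on "with 18 subjects randomized to each of the three intervention groups" and says "we will have 85% power to detect at least a 1.0 standardized effect size", the effect being defined as a "difference in within group means in sd units". The stated conditions are outcomes "measured at 2 time points (baseline and 3-months", a correlation condition ("the intra-class correlation for repeated observations is no greater than 0.5"), and significance level "0.05, two-tailed test". No lower bound, expected value or source is given for the correlation, and no SD of change appears.

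The paragraph then turns to raw units. It assumes that "HbA1c measurements have a standard deviation of approximately 1.5 based on our pilot studies" and repeats the 85% for a change of 1.0 percentage point within each arm. A 10% allowance for missing data and dilution brings 18 per arm to 20.

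Under Data Analysis, the Analysis Plan for Primary Aim states: "The primary framework for analysis is paired t-test". It is applied to the baseline to 3-month change in HbA1c, separately in each arm. The secondary aims use the same test.

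**The concern.** A paired t-test works on the individual change, so its precision depends on how strongly the two measurements are correlated. A high correlation removes between-patient variation and raises power; a low one does the reverse. A condition that the correlation stays at or below 0.5 excludes the values that would help and admits all those that hurt. An upper bound would be conservative for a comparison of averages over the two visits, where the variance is SD²(1 + ρ)/2 and grows with ρ. That analysis is not planned here.

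HbA1c is the primary outcome, and the 1.0-point sentence is the one a reader will use to interpret an arm with no significant change. If the true power is well under 85%, such a result could be wrongly taken as evidence against a 1-point change.

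**Working it through.** **Inputs, all from the Sample Size and Power paragraph:** n = 18 per arm (20 after the allowance); α = 0.05 two-sided; measurement SD = 1.5; raw effect 1.0 point; standardized effect 1.0; correlation ρ ≤ 0.5. The test is the paired t-test from the Analysis Plan for Primary Aim. Values of ρ below 0.5 are assumed scenarios inside the range that the protocol allows.

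**Formulas.**
- SD of change = SD × √(2(1 − ρ)).
- Noncentrality δ = effect × √n / SD of change.
- Power (t): probability that a noncentral t with n − 1 degrees of freedom and noncentrality δ exceeds the two-sided critical value.
- Power (z): approximately Φ(δ − 1.96).

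**Step 1: trying to reproduce 85%.** With the planned test at n = 18, two-sided, ρ = 0.5, neither statement gives 85%:
- 1.0 point: SD of change = 1.5 × √(2 × 0.5) = 1.5; δ = 1.0 × √18 / 1.5 = 2.83; power 76.0% (t) or 80.7% (z).
- 1.0 measurement SD (1.5 points): δ = 1.5 × √18 / 1.5 = 4.24; power 97.9% (t) or 98.9% (z).

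Some other settings do come close to 85%, but none does so for both statements:

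| Effect | Setting | Power |
|---|---|---|
| 1.0 SD | paired z, n = 18, ρ = 0 | 85.1% |
| 1.0 SD | paired t, n = 20, ρ = 0 | 85.1% |
| 1.0 SD | two-sample z, 18 per arm | 85.1% |
| 1.0 point | paired z, n = 20, ρ = 0.5 | 84.7% |
| 1.0 point | paired t, one-sided, n = 18, ρ = 0.5 | 85.7% |

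**Step 2: power by correlation (paired t, n = 18, two-sided).**

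| ρ | SD of change | Power, 1.0 point | Power, 1.0 measurement SD |
|---|---|---|---|
| 0 | 2.121 | 47.1% | 80.7% |
| 0.3 | 1.775 | 61.6% | 92.2% |
| 0.5 | 1.500 | 76.0% | 97.9% |
| 0.6 | 1.342 | 84.6% | 99.4% |
| 0.7 | 1.162 | 93.0% | 99.9% |

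Both power columns rise with ρ, so the end of the range that needs guarding is the low one.

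**Step 3: what 85% for 1.0 point would need.** At n = 18 the t-test needs an SD of change of about 1.334, so ρ = 1 − (1.334/1.5)²/2 = 0.60. With all 20 per arm it needs ρ of about 0.55, and power at ρ = 0.5 is 80.7%. Both correlations lie outside the stated range. Holding ρ fixed instead, 85% needs 23 per arm at ρ = 0.5, 31 at 0.3 and 43 at 0.

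**Step 4: the two 85% statements compared.** With SD 1.5, 1.0 point is 1.0/1.5 = 0.67 SD, while 1.0 SD is 1.5 points. At the same n, α and ρ, two effects of different size cannot have the same power. At ρ = 0.5 the gap is 76% against 98%.

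**The case against.** Four points can be made for the protocol.

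**The correlation condition follows the standardized statement, not the 1.0-point one.** If SD there means measurement SD, 85% is close to the lowest power over ρ from 0 to 0.5: 80.7% by t and 85.1% by z at ρ = 0. If it means the SD of change, ρ does not enter at all and power is about 98%. This stands. A reader might infer that capping the correlation makes every stated 85% a best case. The documents do not support that: 85% is near the floor for 1.0 measurement SD, and for 1.0 point it lies above anything the t-test attains in the range.

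**The shortfall at ρ = 0.5 is not caused by the direction of the bound.** This also stands. The 76% at that value comes from treating 0.67 SD as if it were 1.0 SD. The bound explains only the further fall below 76%. Reversing the inequality would leave the two statements in conflict.

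**With 20 per arm and a normal approximation, ρ = 0.5 gives 84.7% for 1.0 point.** That is true, but the protocol ties its power to 18, keeps the extra two as an allowance for missing data and dilution, and plans a t-test. Even then, 85% is met only at the most favourable correlation permitted.

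**The low correlations are hypothetical.** The protocol gives no estimate, so 47% and 62% are scenarios. A reader might infer that the trial's real power is near 50%, or that the cap was meant as a safeguard and misfired. The text supports neither inference. It does admit those correlations without saying what they do to power.

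**Conclusion.** The concern holds in a limited form. For the planned within-arm paired test, the correlation is bounded on the side that does not protect power, and nothing elsewhere in the protocol corrects this. For 1.0 HbA1c point, the stated 85% is not reached by the planned t-test at any correlation in the stated range. The maximum is 76% with 18 per arm (81% by normal approximation, or 81% by t with all 20), and power is lower for any smaller correlation. Separately, the two 85% statements are incompatible.

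These conclusions rest on reading 1.5 as the SD of the measurements, as the protocol words it, and on a two-sided test. Reading 1.5 as the SD of change would not rescue the 1.0-point figure: it equals the SD of change at ρ = 0.5 and gives the same 76%. The shortfall should not be extended to the 1.0-SD statement, whose power is about 81% to 98% on the measurement-SD reading.

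**What to change.** In the Sample Size and Power paragraph:

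1. Replace the upper limit on the correlation with a justified minimum, or give an SD of change directly. The pilot studies cited for the SD are the natural place to look. The protocol itself offers no basis for any particular minimum.
2. Say whether the standardized effect is in units of the measurement SD or the SD of change.
3. State the power for 1.0 point separately from that for 1.0 SD. With n = 18 and a correlation of 0.5, the 1.0-point figure is 76%.
4. Add a sensitivity row for 1.0 point at correlations of 0.3, 0.5 and 0.7: 62%, 76% and 93%.

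This takes a few sentences and a small table, and the design and sample size can stay as they are. The downside is that the stated power for the primary outcome becomes less favourable.

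### The 85% power claimed for a 1.0-point within-arm HbA1c change does not follow from the protocol's SD of 1.5; 18 per arm give about 76% at best if that SD is cross-sectional

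*Protocol*

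**What the plan says.** All the inputs are in the Sample Size and Power paragraph of the protocol, which sits under Data Collection Strategy.

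- Size per arm: "with 18 subjects randomized to each of the three intervention groups". This is raised by 10% to 20 per arm (N=60) for missing data and intent-to-treat dilution.
- Standardized claim: "85% power to detect at least a 1.0 standardized effect size (difference in within group means in sd units").
- Correlation: "the intra-class correlation for repeated observations is no greater than 0.5".
- SD: "Assuming that HbA1c measurements have a standard deviation of approximately 1.5 based on our pilot studies".
- Raw-unit claim, made for each arm separately: "the study has 85% power to detect a difference of 1.0 percentage points (raw units) change in HbA1c".
- Significance level 0.05, two-tailed.

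For the continuous secondary and exploratory outcomes the paragraph repeats the standardized claim: they "also have 85% power to detect a standardized effect size of 1.0sd".

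The Data Analysis section makes the primary test a paired t-test of the change in HbA1c from baseline to 3 months, carried out in each arm separately.

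**The concern.** One sample size, one test and one significance level carry the same 85% for two effects that differ by a factor of 1.5. This is the protocol's only power statement for the primary outcome in clinical units, so readers will take from it that a 1.0-point change is detectable with 85% power.

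If the true figure is 76%, the chance of missing a real 1.0-point change in a given arm is about 24%, not 15%. A non-significant arm could then be over-read as an incentive structure that failed. One point also matters inside the trial, because a 1% drop in HbA1c triggers the partial reward in every arm.

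**Working it through.** **Inputs** (Sample Size and Power paragraph; test from the Data Analysis section): n = 18 per arm, or 20 with no losses; SD = 1.5; correlation ρ ≤ 0.5; two-sided α = 0.05; paired t-test within arm.

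**1. The plan's 85% for 1.0 SD.** It can be reproduced by normal approximation in two ways:
- Two groups of 18: Φ(1.0 × √(18/2) − 1.96) = Φ(3 − 1.96) = 85.1%.
- Paired, ρ = 0: the SD of change is √2 SD, so Φ((1/√2) × √18 − 1.96) = Φ(3 − 1.96) = 85.1%.

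The two expressions are identical, so the match does not show which was used. Either way the effect is 1.0 SD, which at SD 1.5 is 1.5 points.

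**2. Conversion.** 1.0 SD = 1.0 × 1.5 = 1.5 points. 1.0 point = 1.0/1.5 = 0.67 SD.

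**3. The raw-unit claim under the planned test.** SD of change = 1.5 × √(2(1 − ρ)), which is 1.5 at ρ = 0.5. At n = 18 the noncentrality is (1.0/1.5) × √18 = 2.83, with 17 degrees of freedom and critical value 2.11.
- n = 18: power 76.0% (normal approximation Φ(2.83 − 1.96) = 80.7%).
- n = 20, no losses: power 80.7%.
- n = 22: 84.6%; n = 23: 86.3%. So 23 evaluable per arm would be needed for 85%.

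**4. Range over the correlations the plan allows**, if 1.5 is the SD of a single measurement (n = 18, paired t-test):

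| ρ | SD of change | Power, 1.0 point | Change detectable with 85% power | Power, 1.0 SD (1.5 points) |
|---|---|---|---|---|
| 0.5 | 1.50 | 76% | 1.12 points | 98% |
| 0.4 | 1.64 | 68% | 1.23 points | 95% |
| 0.3 | 1.77 | 62% | 1.33 points | 92% |
| 0 | 2.12 | 47% | 1.59 points | 81% |

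If 1.5 is already the SD of change, the ρ = 0.5 row applies and the correlation plays no further part.

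**5. What would rescue 85% for 1.0 point at n = 18.** The SD of change would have to be about 1.33, so ρ = 1 − (1.33/1.5)²/2 ≈ 0.60. This is above the stated ceiling of 0.5.

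Two other variants come close, and both depart from the plan. A one-sided test at n = 18 gives 85.7%, but the plan is two-tailed. A normal approximation at n = 20 gives just under 85%, but it spends the allowance for missing data, and the t-test itself gives 80.7%.

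**The case against.** The best defence is that this is a pilot, that the shortfall is moderate (76% to 81% against 85%, or 1.12 points against 1.0), and that neither the sample size nor the analysis need change. All of that stands. It bears on how serious the error is, not on whether the figure is right.

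Three stronger readings are tempting, and the document does not support them.

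- *The 18 per arm came from a two-sample formula mislabelled as within-arm.* The two-sample formula does give 18, but so does a paired normal calculation at correlation 0, which lies inside the stated bound. The protocol names no formula and describes a within-group effect. The number is consistent with a two-sample origin and no more.
- *The 85% for 1.0 SD is itself wrong and should be 98%.* The 98% holds only at correlation 0.5, which the protocol gives as a ceiling. Over correlations 0 to 0.5 the paired t-test gives about 81% to 98%, and 85% falls inside that range. The standardized claims, including the one for the secondary and exploratory outcomes, are therefore under-specified but not shown to be false.
- *The power paragraph should be tied to a between-arm primary analysis.* The Data Analysis section contains none; its primary and secondary tests are all within-arm. Whether there should be one is a separate question.

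**Conclusion.** The raw-unit sentence is wrong as written. With SD 1.5, the same 85% cannot apply to both 1.0 SD and 1.0 point. For a 1.0-point within-arm change, the planned paired t-test has 76% power with 18 evaluable per arm and 81% with all 20, provided the SD of change is 1.5. That holds if 1.5 is the SD of change, or if it is the cross-sectional SD and the correlation is 0.5. On the cross-sectional reading these are upper limits, and power at n = 18 falls to 47% at correlation 0.

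The contradiction needs no assumption beyond the protocol's own SD. The replacement figures depend on which SD is meant and, on the cross-sectional reading, on the correlation. The protocol settles neither.

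**What to change.** Keep N=60 and rewrite the power paragraph:

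1. State whether 1.5 is the SD of a single HbA1c measurement or of the change, and that 1.0 SD equals 1.5 points.
2. Replace the raw-unit claim with about 76% power for a 1.0-point within-arm change, and 85% power for about 1.12 points (n=18, SD of change 1.5, paired t-test, two-sided 0.05).
3. If 1.5 is the cross-sectional SD, add the range: the change detectable with 85% power is 1.23 points at correlation 0.4, 1.33 at 0.3 and 1.59 at 0.
4. State the correlation, and whether a t or normal calculation was used, for the 85% at 1.0 SD.

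The cost is one paragraph and a less favourable stated power. No procedure, analysis or participant number changes.

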## Data Analysis

### Design/Analysis Issues

Analysis sets. The intent-to-treat (ITT) sample, comprising all randomized patients, will be used for the primary analyses. The per protocol/completer sample will comprise subjects who were compliant with protocol requirements and for whom all required measurements over 3-months of follow-up have been made. Analyses will be carried out separately for ITT and per protocol samples to test sensitivity of conclusions to drop-outs/nonadherence. If differences are present between the per protocol and ITT analysis sets, the characteristics of the two analysis populations will be examined to aid in explaining any discrepancies.

**Analysis Plan for Primary Aim (Efficacy):** To test the efficacy of three financial incentive structures in combination with technology intensified diabetes education and skills training intervention on HbA1c levels in AAs with T2DM. Preliminary analyses will be conducted to assess the similarity of the treatment arms based on collected variables. Univariate descriptive statistics and frequency distributions will be calculated, as appropriate for all variables along with two-sided 95% confidence intervals when appropriate. Study discontinuation (attrition) rates will be estimated for each group. The preliminary analyses will describe the pre-specified covariates as well as identify potential confounding (prognostic) variables to be used as covariates in subsequent secondary analyses. Covariates to be examined in the preliminary analyses and potentially used in secondary analyses include age, sex, income, health literacy, social support, depression, and comorbidity. The primary framework for analysis is paired t-test. Change in HbA1c from baseline to 3-months (dependent variable) will be examined in each treatment arm (high, moderate and low frequency of financial incentives) using a type I error rate of 0.05.

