### **Data Collection Strategy**

**Personnel:** Two half-time masters-level trained diabetes educators (DEs) will deliver the interventions; one full-time research assistant (RA) will conduct screening, consent, enrollment procedures, and questionnaire administration; a half-time data entry clerk (DC) will be responsible for data entry; and a part-time masters-level statistician will be responsible for data management (DM). Each potentially eligible patient will be asked to report for a screening visit. At this visit, the following will be collected: basic demographic information, screening information, and a blood sample for a screening hemoglobin A1c (HbA1c) value. Basic demographic information will be collected to compare those screened to those randomized. Individuals who have a screening HbA1c of  $\geq 8$  will be asked to return within two weeks for a baseline visit. At the baseline visit, a full battery of questionnaires will be administered, and individuals will be randomized. All individuals randomized will have follow-up visits at 3 months, where survey questionnaires will be administered, and blood collected for HbA1c. Blood pressure will also be measured at the baseline and 3 months follow-up visit.

**Primary Outcome Measure: HbA1c:** About 10cc of blood will be drawn by trained phlebotomists and sent to the lab for HbA1c.

**Secondary Outcome Measures: Blood Pressure:** Blood pressure readings will be obtained using automated BP monitors (OMRON IntelliSense™ HEM-907XL). The device will be programmed to take 3 readings at 2 minute intervals, and give an average of the 3 BP readings. **Resource Utilization & Cost:** Previously validated questions on resource utilization will be administered. The questionnaires are 1 page long and capture information on hospitalizations, physician/professional visits, and medications. **Quality of Life:** The SF-12 (Ware 1996) is a valid and reliable instrument to measure functional status. The SF-12 items reproduce at least 90% of the variance in PCS-36 and MCS-36 scores.

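### The imputation assumed in the sample size is not carried into the fixed paired t-test, and the named drop-out check uses a sample that contains no drop-outs

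*Protocol*

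**What the plan says.** In the Protocol, Data Analysis, Design/Analysis Issues, the primary set is everyone randomised: "The intent-to-treat (ITT) sample, comprising all randomized patients, will be used for the primary analyses". Under the analysis plan for the primary aim, "The primary framework for analysis is paired t-test" and "Change in HbA1c from baseline to 3-months (dependent variable) will be examined in each treatment arm". The secondary aims use the same test.

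There is one follow-up HbA1c. In Data Collection Strategy: "All individuals randomized will have follow-up visits at 3 months, where survey questionnaires will be administered, and blood collected for HbA1c".

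Sample Size and Power raises 18 per arm by 10% to 20 (60 in all) to allow for missing "information that must be imputed in the ITT sample and the dilution effect of ITT analyses". Neither the primary nor the secondary analysis plan mentions imputation again.

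The check on drop-out is stated as follows: "Analyses will be carried out separately for ITT and per protocol samples to test sensitivity of conclusions to drop-outs/nonadherence". The per-protocol/completer sample consists of "subjects who were compliant with protocol requirements and for whom all required measurements over 3-months of follow-up have been made". If the two sets differ, their characteristics are to be examined. Attrition is to be estimated for each group.

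**The concern.** There are two linked problems.

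The first is that the sample-size section and the analysis section do not fit together. One counts on imputed values. The other fixes a test that needs both members of each pair and does not say what data it is run on. An analyst who follows only the analysis section would report a complete-case result under an ITT label.

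The second is that the named check cannot do its stated job. A sample that excludes drop-outs by definition cannot show what drop-outs would do to the conclusion. It also mixes missingness with non-adherence. Adherence may differ by arm for reasons built into the design: glucose uploads are paid in the Moderate and High Frequency arms, and session attendance in the High Frequency arm only.

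What is at stake is a false reassurance. Missingness related to outcome is plausible here. The end-of-study reward depends on the 3-month HbA1c, with maxima of $300, $170 and $130 in the Low, Moderate and High Frequency arms, and patients measure their own glucose, so some may foresee no reward. The flat $25 for completing the 3-month assessment, paid in every arm whatever the result, works against this but does not exclude it.

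**Working it through.** **Inputs.** From Sample Size and Power: 18 per arm before inflation, 10% inflation, SD 1.5, intra-class correlation at most 0.5, target change 1.0 point, two-sided alpha 0.05. From Data Collection Strategy: one follow-up HbA1c. The protocol forecasts no attrition rate. Its 10% covers both missing information and ITT dilution, so the rates of 10% to 30% below are assumptions.

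**Step 1: the plan's own figure.** 18/(1 − 0.10) = 20.0, and 18 × 1.10 = 19.8, which rounds to 20. The stated 20 per arm reproduces.

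**Step 2: who is in each analysis.**

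| Reading | Primary (ITT) test | Per-protocol test | What the comparison shows |
|---|---|---|---|
| Paired t-test run literally, no imputation | Patients with a 3-month HbA1c | A compliant subset of the same patients | Non-adherence only; drop-outs are in neither |
| Paired t-test on imputed data | All 20 per arm | Compliant completers | Non-adherence and removal of drop-outs together, under one fixed imputation assumption |

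In the second row the two results can agree simply because imputed values are predicted from relations fitted to patients who stayed. No assumption about the missing values is varied, so the check fails its purpose under both readings.

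**Step 3: size of the possible shift.** Assume completers change by −1.0 and patients with a missing value by 0. With a proportion p missing, the all-randomised mean change is −(1 − p) × 1.0.

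- p = 10%: (18 × −1.0 + 2 × 0)/20 = −0.90
- p = 20%: −0.80
- p = 30%: −0.70

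The complete-case mean stays at −1.00 throughout.

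**Step 4: scale.** The SD of change is 1.5 × √(2 × (1 − 0.5)) = 1.5 at the intra-class correlation limit. With 18 pairs the standard error is 1.5/√18 = 0.35, so the 0.10 shift at 10% missing is 0.10/0.35, or about 0.28 of a standard error.

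**Step 5: false positives if missingness follows outcome.** In a simulation of single arms of 20 with no true change and SD 1.5, the odds of a missing value were multiplied by e per SD of worsening (an assumption). The unimputed paired t-test gave:

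| Average missing | Mean change in those observed | Rejection rate (nominal 5%) |
|---|---|---|
| 13% | −0.18 | 7% |
| 24% | −0.31 | 12% |
| 33% | −0.41 | 17% |

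**Step 6: power lost if pairs are dropped.** For a 1.0-point change with SD of change 1.5, the paired t-test (noncentral t) has power 0.81 with 20 pairs, 0.76 with 18, 0.70 with 16 and 0.64 with 14.

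**The case against.** The strongest reply is that the protocol does commit to imputation. Read with the sample-size section, the plan is all randomised patients, imputation, then a paired t-test, and such a test can use all 60. The imputation model, auxiliary variables and delta values are commonly left to a statistical analysis plan, which may exist but is not shown. This reply stands in part. A reader might infer that the primary analysis is a complete-case analysis and drops every patient without a 3-month value. The document does not prove that, because it says missing values must be imputed. The absence of a named imputation method is also no finding in itself.

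The reply does not rescue the drop-out check, which the protocol itself names and fixes. With imputation in place, the completer comparison still contains no drop-outs and varies no assumption about them. Estimating attrition by group and comparing the characteristics of the two sets are useful description, but they do not show how the conclusion would change.

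Three further limits are fair. At 10% missing the shift is under a third of a standard error, in a self-described pilot. The protocol does not define compliance as uploading or attending, so selection by arm is possible but not shown. A reader might also infer that unequal loss would hide a difference between arms. The plan makes no between-arm estimate, so no such reported figure exists to be biased.

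**Conclusion.** The point holds in two parts. First, the sample-size and analysis sections need to be joined: the primary set is all randomised, imputation is assumed in the sizing, and the fixed test says nothing about it. Second, and independently, the comparison named as the test of sensitivity to drop-out cannot serve that purpose.

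The size depends on assumptions the protocol does not supply. If completers fall by 1.0 point and drop-outs are unchanged, the gap is 0.10 points at 10% missing and 0.30 at 30%. If missingness follows worsening as strongly as assumed above, the false-positive rate of an unimputed test rises to between 7% and 17%. At the low end this is modest. The correction is worth making before analysis because the planned check would not reveal either the low or the high end.

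This point does not call for replacing the paired t-test with a between-arm model. That is a separate question, and multiple imputation is compatible with the paired test.

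**What to change.** 1. In the analysis plan for the primary aim, state that the within-arm paired analysis of change is run on all 60 randomised patients after multiple imputation by arm, using baseline HbA1c, session attendance and uploaded glucose. All of these are already collected. With 20 patients per arm the imputation model should be kept small. Apply the same statement to the secondary outcomes.

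2. In Design/Analysis Issues, replace the completer comparison as the drop-out check with two analyses: (a) missing 3-month HbA1c set to the patient's baseline value; (b) imputed values shifted by a delta chosen separately for each arm, over a stated range. In the illustration, (a) returns 0.90 directly. For (b), a shift of delta moves an arm's mean by p × delta, so 10% missing and a shift of 1.0 point gives −1.00 + 0.10 = −0.90. These checks are needed as well as step 1, because imputation that relies on observed data need not recover 0.90 if drop-outs differ in ways those data do not predict.

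3. Keep the per-protocol result, labelled as descriptive for non-adherence.

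The cost is a few sentences of protocol text and a little more analysis work. No new data are needed. The estimate may be slightly less favourable.
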